The sample size is estimated to attain adequate power to determine the effects of treatment preferences on attrition, adherence, and sleep outcomes. Sample size estimation also considers the repeated measure feature of the design. Within-subject designs require a smaller number of participants than between-subject designs, to achieve the same statistical power [30]. A medium sized effect (0.5) is anticipated on the basis of: 1) results of a systematic review showing that behavioral therapies had moderate-to-large effects on sleep parameters (sleep onset latency and wake after sleep onset) in middle-aged and older adults [31]; and 2) an expected medium effect for the comparison of participants assigned to treatment randomly or congruent with their preferences. A medium effect is anticipated, rather than a small effect as reported in the literature, with the use of a reliable and valid measure of treatment preferences. Applying Cohen’s [32] criteria for an anticipated medium effect size for the main comparison, the inclusion of four groups (i.e. participants allocated to the stimulus control therapy and those allocated to the sleep restriction therapy either randomly or based on their preference), and setting α at .05 and β at .80, the required sample size is 60 per group, for a total of 240 participants to be recruited.

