### Data analysis

In addition to descriptive statistics to characterize the participants in terms of their demographic and clinical characteristics, the following analyses are planned to address the study objectives:Objective 1: Chi-square test will be used to compare the number of participants who withdrew from the study across the four study groups defined by the type of treatment received (stimulus control therapy and sleep restriction therapy) and the method of allocation to treatment (random and preference). One-way analysis of variance will be applied to examine differences in level of adherence (i.e. attendance to treatment sessions and enactment of treatment recommendations), and the pattern of change (estimated with a slope) in the sleep outcomes, across groups.Objective 2: Chi-square test will compare the number of dropouts between participants in the random arm who receive matched and mismatched treatment. Independent samples t-test will examine differences between the matched and mismatched subgroups in levels of adherence (exposure and enactment) to treatment and the pattern of change in the sleep outcomes.

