Despite its advantages, there are some challenges in carrying out a two-stage PRCT. The first challenge relates to the first stage of randomization. Through the process of obtaining informed consent, participants are informed of the two stages and of the method for treatment allocation within each arm. Participants with strong treatment preferences may be unwilling to leave treatment choice to chance and they may desire allocation to the preference arm. If randomized to the random arm, they may react unfavorably [4] and withdraw from the study.

The second challenge in the implementation of the two-stage PRCT relates to the method of treatment allocation applied in the second stage of the trial. At this stage, participants in the random arm are randomized to treatment, yielding a balanced number of participants assigned to the treatment groups. However, the equality of the treatment groups’ sizes is not achieved in the preference arm if most participants choose one treatment over the other. Large differences in group sizes may yield unequal within-group variances; if not addressed with appropriate statistical formula, unequal variances may reduce the power to detect significant treatment and preference effects [35]. The validity of these conclusions is further jeopardized if the pretest comparability of participants is not maintained. Randomization to treatment, applied in the random arm, increases the likelihood of achieving baseline comparability. However, such comparability may not be observed in the preference arm due to possible differences in the profile of participants choosing the alternative treatments under evaluation. Therefore, the baseline comparability of participants assigned to the different treatments randomly or by preference is not maintained, potentially confounding the results.

The third challenge in conducting the two-stage PRCT relates to the reactions of participants assigned to treatment on the basis of chance or preference. Specifically, participants in the random arm may have preferences for the treatments under investigation. Those randomized to the non-preferred treatment may react unfavorably. In contrast, participants in the preference arm may react favorably because they get the treatment they desire. These reactions may influence the participants’ adherence and responses to the allocated treatment.

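### The Objective 1 ANOVA does not carry through the unequal-variance safeguard that the Discussion calls for; if preference-arm sizes and variances differ together, its type I error can move either way from .05

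*Protocol article*

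**What the plan says.** **Data analysis, Objective 1.** Adherence (sessions attended and enactment) and the slopes of the sleep outcomes are compared across four groups: two therapies, each reached by chance or by choice. The method is given as "One-way analysis of variance will be applied to examine differences in level of adherence", and the same sentence extends it to the slopes. The section names no unequal-variance version and no rule for using one.

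**Sample.** The calculation rests on "setting α at .05 and β at .80" and on equal groups: "the required sample size is 60 per group, for a total of 240 participants to be recruited".

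**Discussion, second challenge.** For the random arm, the article describes assignment as "yielding a balanced number of participants assigned to the treatment groups". For the other arm it says that "the equality of the treatment groups’ sizes is not achieved in the preference arm if most participants choose one treatment over the other". It adds that large differences in size may go with unequal variances, and that "if not addressed with appropriate statistical formula, unequal variances may reduce the power to detect significant treatment and preference effects".

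**The concern.** The article names a hazard and a type of remedy in its Discussion, then names a test in its analysis section whose usual form assumes equal variances. Nothing connects the two.

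The consequence that the Discussion gives is also incomplete. When group sizes and variances differ together, the classical F test may lose power, but it may also reject a true null hypothesis more or less often than the nominal 5%. A reader of the Discussion alone could take a significant Objective 1 result as safe and worry only about non-significant ones. Objective 1 carries the comparison of random with preference-based allocation, so a false positive there would be read as an effect of preference.

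**Working it through.** **1. The plan's own figure.** Inputs from the Sample section: α = .05; the value .80 attached to β, read as power; an effect of 0.5 described as medium; four groups; 60 per group.

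- Four-group F test with Cohen's medium f = 0.25: 45 per group for 80% power (60 per group gives 91%).
- Two groups with d = 0.5, two-sided: n = 2(1.960 + 0.842)²/0.5² = 62.8, so 63 per group (64 with the t distribution).

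Neither gives exactly 60. That is a separate matter. Here 60 per group, hence 120 per arm, is taken as the planned design.

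**2. Why the level moves.** With group sizes nᵢ, total N and k = 4, the classical statistic is

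F = [Σ nᵢ(mᵢ − m)²/(k − 1)] / [Σ (nᵢ − 1)sᵢ²/(N − k)].

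Under equal means the numerator has expectation Σ σᵢ²(1 − nᵢ/N)/(k − 1) and the denominator Σ (nᵢ − 1)σᵢ²/(N − k). With equal variances both equal σ², whatever the sizes. With sizes 60/60/84/36 and an SD of 1 except where stated:

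- Smaller preference cell at SD 1.5: numerator (0.75 + 0.75 + 0.65 + 2.25 × 0.85)/3 = 1.354; denominator (59 + 59 + 83 + 35 × 2.25)/236 = 1.185; ratio 1.14. F runs too high.
- Larger preference cell at SD 1.5: numerator (0.75 + 0.75 + 2.25 × 0.65 + 0.85)/3 = 1.271; denominator (59 + 59 + 83 × 2.25 + 35)/236 = 1.440; ratio 0.88. F runs too low.

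**3. Size by simulation.** Normal data, equal means, nominal .05, 200,000 replicates per scenario (Monte Carlo standard error about √(.05 × .95/200,000) = .0005). The random arm is 60/60 and one preference cell has the different SD. The preference splits and SD ratios are assumptions, because the article gives none. Entries are rejection rates of classical ANOVA: smaller cell more variable / larger cell more variable. In the 60/60 row the two entries simply name one or the other preference cell.

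| Preference split | SD ratio 1 | 1.25 | 1.5 | 2 |
|---|---|---|---|---|
| 60/60 | .0503 / .0507 | .0521 / .0511 | .0555 / .0555 | .0666 / .0664 |
| 72/48 | .0499 / .0510 | .0575 / .0454 | .0674 / .0451 | .0876 / .0475 |
| 84/36 | .0500 / .0494 | .0634 / .0411 | .0824 / .0371 | .1180 / .0336 |
| 96/24 | .0499 / .0504 | .0715 / .0364 | .0996 / .0286 | .1545 / .0230 |
| 102/18 | .0483 / .0496 | .0758 / .0336 | .1083 / .0251 | .1754 / .0186 |

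If the different SD goes with the therapy, so that it applies in both arms, the direction is the same and the shift mostly smaller. At 84/36 the rates are .0632, .0761 and .0959 for ratios 1.25, 1.5 and 2 when the therapy with the smaller preference cell is more variable.

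**4. The alternative.** Welch's ANOVA weights each group by wᵢ = nᵢ/sᵢ² and does not pool variances. Across all these scenarios it rejects in .049 to .052 of trials.

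**5. Its cost.** With equal variances and a shift of 0.5 SD in both preference groups, power (classical / Welch) is 91.2% / 91.0% at 60 per group and 91.4% / 90.8% at 60/60/96/24. The loss is 0.2 and 0.6 percentage points.

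**The case against.** **The test name may already cover Welch.** The article says one-way analysis of variance and does not say pooled variance. It condenses a fuller protocol, and the variance version could be set in a plan that is not shown. The two sections are therefore compatible. This stands as a limit: the article cannot be said to rule Welch out. It does not remove the point, because the article itself calls for a suitable formula and then names a test that is normally taken in its equal-variance form.

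**The hazard is conditional.** A reader might infer that the article expects unequal sizes and variances, and so that the .05 level is not held. The documents do not support that. The Discussion speaks of what follows if most participants choose one therapy, and of variances that may differ. Unequal sizes alone leave the level at about .05 even at 102/18. The article does not say which cell would be more variable, and both preference cells are self-selected. Nor does the point hold for every continuous outcome: where variances are similar, nothing is wrong.

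**The t-test.** A reader might extend the point to the t-test of Objective 2. It does not carry over. That test compares matched with mismatched participants within the random arm, which the article describes as balanced. If 60 are assigned to each therapy and a share p prefers one of them, the expected number matched is 60p + 60(1 − p) = 60 of 120, whatever p is. At such sizes Student's t holds its level (5.1% at 60 v 60 with an SD ratio of 1.5).

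**The Discussion is not false.** Loss of power is a real consequence, as the conservative right-hand entries in the table suggest, and the Discussion goes on to mention validity. But it does so for baseline comparability, not for the error rate of the test. Its statement is incomplete, not wrong.

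**Normal data.** The simulation does not represent attendance, which is a count out of two sessions. The figures apply best to slopes and to weekly enactment percentages. This limit stands.

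**Conclusion.** The point holds as a gap between two sections of the article. The analysis for Objective 1 does not carry through the safeguard that the Discussion calls for, and the Discussion leaves out type I error.

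If preference-arm sizes and variances differ together, classical ANOVA at nominal 5% rejects a true null hypothesis in about 6 to 12% of trials at 84/36 and 7 to 15% at 96/24 when the smaller cell has 1.25 to 2 times the SD. When the larger cell has 1.5 times the SD, it rejects in about 3 to 4%. The upper ends need a doubled SD in one cell; at 84/36 with a ratio of 1.25 the rate is 6.3%.

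These figures rest on assumed splits, assumed SD ratios, normal data and 240 participants analysed. They do not show that this trial's error rate is off. The point is limited to the Objective 1 ANOVA.

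**What to change.** In Data analysis, Objective 1, name Welch's ANOVA in place of one-way analysis of variance for adherence and outcome slopes. If the full analysis plan already specifies it, a reference to that is enough. In the Discussion, add that unequal variances combined with unequal group sizes can change the type I error as well as the power. The Objective 2 t-test needs no change on this ground.

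The cost is one line of analysis wording and one clause in the Discussion, with a power loss of under one percentage point if variances turn out equal. The article describes 12-month data collection as still in progress, so the choice can be recorded before the final analysis. For session attendance, whose few possible values could leave a cell with no variance, the plan should check that the chosen test can be computed.

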**Fig. 1 Fig1:**
[figure not shown]
Illustration of the PRCT design

The treatments investigated in the current study are two behavioral therapies that demonstrated efficacy in the management of chronic insomnia: stimulus control therapy and sleep restriction therapy [25]. Eligible consenting participants complete the pretest questionnaire measuring socio-demographic and clinical characteristics, sleep outcomes, perception of the treatments’ attributes and preferences for the behavioral therapies. Participants are randomized to the two trial arms, using sealed opaque envelopes. Participants in the random arm are randomly assigned to the stimulus control therapy or the sleep restriction therapy, using sealed envelopes. Participants in the preference arm are allocated to the treatment they indicate that they prefer. Participants expressing no preferences are randomly assigned to treatment. The outcomes are assessed at four points in time: pretest (i.e. within 2 weeks before treatment); post-test (i.e. within 1 week after treatment completion); 6-month and 12-month follow-up. Data on adherence to treatment are collected prospectively, during the treatment and post-treatment periods. Three strategies are used to minimize attrition: reimbursement for travel expenses to attend the data collection and the treatment sessions, a $10 gift certificate, and telephone call reminders. The calls are made to all participants within 1 week prior to the planned research activity (i.e. attendance at treatment session and data collection).

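### The sleep-outcome slopes are compared without the pretest value as covariate, which gives up precision in the randomised contrasts

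*Protocol article*

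**What the plan says.** Under Data analysis, Objective 1 uses a one-way ANOVA over four groups, formed by treatment received and method of allocation. The ANOVA covers adherence and "the pattern of change (estimated with a slope) in the sleep outcomes, across groups". For Objective 2, within the random arm, the article states: "Independent samples t-test will examine differences between the matched and mismatched subgroups". This covers adherence and the pattern of change in sleep outcomes. No covariate or baseline adjustment is mentioned in that section or elsewhere in the article.

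The Design section says: "The outcomes are assessed at four points in time: pretest", then post-test, 6 months and 12 months. It also says that pretest data are obtained before participants are randomised to the two arms.

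The Discussion, on the second challenge of the design, says that in the preference arm people choosing different treatments may differ in profile. It concludes that "the baseline comparability of participants assigned to the different treatments randomly or by preference is not maintained, potentially confounding the results".

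**The concern.** The pretest value is available for everyone randomised and is measured before allocation, which makes it a safe covariate in any randomised comparison. It is also related to the quantity analysed. A slope whose first point is the pretest value tends to be more negative when that value is high and more positive when it is low. The named tests leave that predictable variation in the error term.

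What is at stake is power and interval width. The Sample section justifies the sample size partly by the efficiency of repeated measurement, and the meta-analytic preference effects cited in the Background are small (.15 and .31). Precision given up at the analysis stage therefore matters.

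**Working it through.** **The plan's own sample size, for context.** The Sample section states "A medium sized effect (0.5) is anticipated", "setting α at .05 and β at .80" (the .80 read here as power) and "the required sample size is 60 per group, for a total of 240 participants to be recruited". The two-sided two-group formula gives n = 2(1.96 + 0.84)²/0.5² = 63 per group (64 by exact t). A four-group ANOVA at f = 0.25 gives 45, and a one-sided comparison gives 50. None of these is 60, and no dropout allowance is stated. That is a separate matter. Here 60 per group is used only as the reference size.

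**Inputs for the slope check.**
- Visits: pretest, post-test, 6 and 12 months (Design). The times 0, 1.25, 6 and 12 months are assumed, with post-test about five weeks after the start (four weeks of treatment plus one). The article does not say how time is coded, so equal spacing (0, 1, 2, 3) is also tried.
- Correlation between visits: not given. A common value ρ of .3, .5 or .7 with equal variances is assumed. The diary's test-retest reliability (.69 to .93) is not a pretest-to-follow-up correlation.

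**Formula.** The least-squares slope has weights c_j = (t_j − t̄)/S, with S = Σ(t_j − t̄)². These sum to zero. With unit variances and common correlation ρ:
- Var(slope) = (1 − ρ)/S
- Cov(slope, pretest) = (1 − ρ)(t₀ − t̄)/S
- Corr(slope, pretest) = √(1 − ρ) × (t₀ − t̄)/√S

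The share of slope variance removed by adjustment is R² = Corr².

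**Numbers.**
- Calendar time: t̄ = 19.25/4 = 4.8125 and S = 88.92, so (t₀ − t̄)/√S = −4.8125/9.430 = −0.510 and R² = 0.260(1 − ρ).
- Equal spacing: t̄ = 1.5 and S = 5, so R² = (2.25/5)(1 − ρ) = 0.45(1 − ρ).

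The equivalent n is 60(1 − R²), rounded up. Power is Φ(0.5√(60/2)/√(1 − R²) − 1.96), for a difference of 0.5 unadjusted slope-SD and 60 per group. Without adjustment it is Φ(2.739 − 1.96) = 0.78.

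| Coding | ρ | Corr | Variance removed | n matching 60 unadjusted | Power |
|---|---|---|---|---|---|
| Calendar | .3 | −.43 | 18% | 50 | .86 |
| Calendar | .5 | −.36 | 13% | 53 | .84 |
| Calendar | .7 | −.28 | 8% | 56 | .81 |
| Equal | .3 | −.56 | 32% | 42 | .91 |
| Equal | .5 | −.47 | 23% | 47 | .88 |
| Equal | .7 | −.37 | 14% | 52 | .84 |

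**Which contrasts are randomised.** Treatment within the random arm is randomised. So is matched against mismatched, because for a participant with a given preference the match is decided by the random assignment. Whole random against whole preference arm is protected by the first-stage randomisation. The cells that chose a treatment are not randomised against the other cells.

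**What adjustment does in the self-selected cells.** Take a 0.3 SD pretest difference and no true effect, at ρ = .5 in calendar time.
- *The difference is stable, the same at every visit.* The slope weights sum to zero, so the expected unadjusted slope difference is 0. Adjustment subtracts −.36 × 0.3 and so creates a difference of about 0.11 slope-SD.
- *The difference acts only through the pretest value and regresses away.* The unadjusted contrast is shifted by .36 × 0.3 = 0.11 slope-SD, and adjustment removes the shift.

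The two errors are equal in size. They range from 0.13 to 0.08 slope-SD over ρ = .3 to .7 in calendar time, and from 0.17 to 0.11 with equal spacing.

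**The case against.** **A stronger reading is tempting.** A reader might infer that leaving out pretest biases the comparison of self-selected groups, and that ANCOVA would correct it. The documents do not support this. A slope that includes pretest already removes a stable level difference. The Discussion speaks of differences in the profile of people who choose each treatment, and such differences may well be stable. In that case the unadjusted slope is the unbiased one and adjustment introduces the error (Lord's paradox). If the difference is transient, the reverse holds. The article does not say which applies. This objection stands, and it limits the point mainly to precision.

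**Larger savings might be quoted** by setting ANCOVA against a simple change score (25% at one visit with ρ = .5). The plan analyses slopes, so that figure does not describe it.

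**The inputs are assumed.** This also stands. Visit coding alone moves the gain from 8–18% to 14–32%. Diaries are also kept during treatment, and the article does not say which time points enter the slope. The direction of the gain does not depend on the exact value: under the common-correlation model the slope is negatively correlated with pretest for any ρ below 1.

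**An article may leave covariates to a fuller plan.** Often so, but this one names specific tests that take no covariate and fixes them for both objectives. If a fuller plan adjusts for pretest, the two texts need reconciling.

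**Chance imbalance in randomised contrasts** is already covered by the nominal 5% error of an unadjusted test. That is correct: the loss there is of precision, not validity.

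**Conclusion.** The point holds as a loss of precision. The named tests leave out a covariate that is already collected before randomisation and is correlated with the slope. Under a common between-visit correlation of .3 to .7, adjustment removes about 18% to 8% of slope variance with visits at 0, 1.25, 6 and 12 months, or 32% to 14% with equally spaced coding. At 60 per group and a difference of 0.5 slope-SD, two-group power rises from about .78 to between .81 and .91. For Objective 2, 60 per subgroup is what would be expected if all 120 random-arm participants state a preference. With fewer, power is lower, but the proportional variance reduction is the same.

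The gain is clear for the three randomised contrasts. For Objective 1 contrasts involving the preference-arm cells, the protocol article concedes non-comparability, but it does not follow that the unadjusted slope is the wrong analysis or that the adjusted one is right. Neither removes confounding by other characteristics of those who choose. The change is worth making, but its absence does not invalidate the plan.

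**What to change.** In Data analysis, for both objectives, add the pretest value of the same sleep outcome as a covariate to the slope comparison (a linear model in place of the plain ANOVA and t-test). Alternatively, model the post-test, 6-month and 12-month values by ANCOVA or a mixed model with pretest as covariate. This alternative changes the quantity estimated, so the variance figures above do not carry over to it. State which visits enter the slope and how time is coded.

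Make the adjusted analysis the main one for matched against mismatched, for treatment within the random arm, and for whole random against whole preference arm. For Objective 1 contrasts that involve the preference-arm cells, report pretest-adjusted and unadjusted slope results side by side as sensitivity analyses. Say that neither is unbiased in general and that adjustment does not remove the confounding.

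The cost is analysis wording only: no new data, visits or participants. The article describes the 12-month follow-up as still being collected, so the change could be fixed before the final analysis.
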